## Abstract

**Aim:**

Chronic heart failure (HF) is a frequent comorbidity in elderly patients undergoing major non-cardiac surgery with increasing prevalence. This trial aims to evaluate a new interdisciplinary, multimodal and individually optimised treatment strategy in patients with established or at risk for HF throughout the entire perioperative period.

**Methods:**

The PeriOP-CARE HF trial is a prospective, multicentre, randomised, controlled and interventional trial. The primary hypothesis is that an interdisciplinary, intersectoral and standardised approach to the preoperative evaluation, optimisation and perioperative management of patients aged ≥ 65 years undergoing non-cardiac surgery with intermediate or high surgical risk and preoperative N-terminal pro-brain natriuretic peptide levels ≥ 450 pg/mL, will reduce postoperative morbidity. The preoperative evaluation includes clinical evaluations by anaesthesiologists and cardiologists, electrocardiography and echocardiography, as well as a discussion of these findings by a perioperative management team, where all involved specialities, including the speciality surgeon, will decide the perioperative treatment strategy for each patient. Intraoperative strategies include individualised haemodynamic optimisation. The interdisciplinary team and specialised HF nurses will screen patients for HF-related postoperative complications. The primary end point will be a composite morbidity end point, comprising any rehospitalisation, acute kidney injury, suspected or proven bacterial infection requiring treatment and acute decompensated HF at postoperative day 90.

**Conclusion:**

The new treatment form can potentially reduce the morbidity burden after major non-cardiac surgery in patients with known or unknown HF. If the PeriOP-CARE HF trial yields positive results, the treatment of patients with HF undergoing major non-cardiac surgery could be considerably improved.

**Trial Registration:**

clinicaltrials.gov: NCT06381427, registered April 24, 2024.

**Supplementary Information:**

The online version contains supplementary material available at 10.1007/s00392-025-02626-3.

## Introduction

Chronic heart failure (HF) is a frequent comorbidity in elderly patients undergoing major non-cardiac surgery [1]. Its overall prevalence is increasing in ageing populations, and its prevalence in patients aged > 65 years is currently estimated at > 10% [2]. Chronic HF is associated with increased postoperative morbidity and mortality. A recent observational study revealed that the incidence of postoperative acute HF is approximately 2.5%, leading to markedly elevated mortality rates of up to 44% [1]. Furthermore, half of the patients with postoperative acute HF are not diagnosed with HF preoperatively. These findings not only indicate the need for careful management of patients with HF requiring non-cardiac surgery but also emphasise the need to identify patients with undiagnosed HF who might be at even greater risk for perioperative complications.

Current European Society of Cardiology (ESC) guidelines on the cardiovascular assessment and management of patients undergoing non-cardiac surgery recommend that patients undergoing major non-cardiac surgery should be carefully examined for signs of HF. However, diagnosing HF based solely on patient’s history and physical examination may be challenging during the preoperative evaluation [3]. Measuring preoperative cardiac biomarkers, such as natriuretic peptides, might help identify patients with unknown HF, assess their perioperative risk and predict their risks of mortality, stroke and cardiovascular adverse events [4]. Therefore, measuring the N-terminal pro-brain natriuretic peptide (NT-pro-BNP) level has a Class IIa recommendation for patients with known cardiovascular disease, cardiovascular risk factors or symptoms suggestive of cardiovascular disease undergoing non-cardiac surgery with intermediate or high surgical risk. Although routine NT-pro-BNP assessment is currently not recommended (Class III recommendation), natriuretic peptides have generally been shown to effectively predict major cardiac adverse events after major non-cardiac surgery in different patient populations [5–8].

Nevertheless, clinically applicable cut-offs triggering distinct actions are lacking, and current guidelines do not recommend any specific perioperative treatment strategies in patients that could be directly derived from a certain preoperative NT-pro-BNP measurement [3, 9]. Therefore, the current European Society of Anaesthesiology and Intensive Care-focused guideline for using cardiac biomarkers in perioperative risk evaluation limits preoperative NT-proBNP-derived management to clinical research because insufficient clinical data are available [9]. Since most postoperative HF-related complications occur during the first days after surgery, optimisation of patients should already begin preoperatively and should be followed by adequate intra- and post-operative management [10].

Therefore, the PeriOP-CARE HF trial aims to combine systematic preoperative screening using a new NT-proBNP cut-off with a standardised preoperative evaluation to provide interdisciplinary, multimodal and individually optimised treatment throughout the entire perioperative period.

## Study design

The PeriOP-CARE HF trial is a prospective, multicentre, randomised, controlled, interventional trial that will be conducted at six university hospitals in Germany: Berlin (Charité, Campus Benjamin Franklin), Giessen, Hamburg, Herne, Würzburg and Rostock. All trial activities will be conducted according to the relevant guidelines and regulations, such as the Declaration of Helsinki and the Good Clinical Practice guidelines. Informed consent to participate will be obtained from all subjects before any trial-specific activities.

The primary hypothesis is that an interdisciplinary, intersectoral and standardised approach to the preoperative evaluation, optimisation and perioperative management of patients aged ≥ 65 years undergoing non-cardiac surgery with intermediate or high surgical risk and preoperative NT-proBNP levels of ≥ 450 pg/mL, regardless of preoperative known or unknown HF status, will reduce postoperative morbidity (Fig. 1).

**Fig. 1 Fig1:**
[figure not shown]
Study flowchart

This trial has been approved by the Local Ethics Committee of the Faculty of Medicine at Justus Liebig University Giessen, Germany (approval number: AZ 73/22), as the primary ethical review board for this trial, and all participating centres will obtain approval from their local responsible ethics committees according to individual legislation requirements. This trial has received a full public grant from the Innovationsfonds of the Gemeinsamer Bundesausschuss (grant no. 01NVF22109). The enrolment of the first patient is planned for the end of 2024, and the last patient is expected to complete the follow-up by the mid of 2026. This trial is registered at ClinicalTrials.gov in April 2024 (NCT06381427).

### Study population

The study population will comprise patients aged > 65 years with American Society of Anesthesiologists classification II or higher who will undergo elective major non-cardiac surgery under general anaesthesia. Surgical risk will be assessed according to the current 2022 ESC guidelines on the cardiovascular assessment and management of patients undergoing non-cardiac surgery, and only patients with intermediate or high surgical risk will be included [3]. The exclusion criteria include surgery with an approximated duration of less than 30 min, transplant surgery and other criteria that might interfere with the chosen end points. The inclusion and exclusion criteria are summarised in Table 1.

**Table 1 Tab1:** Inclusion and exclusion criteria

Inclusion criteria	Exclusion criteria
Age ≥ 65 years	Incision suture time < 30 min
Elective non-cardiac surgery with intermediate or high surgical risk under general anaesthesia	Surgery with general anaesthesia within the past 30 days
ASA ≥ II	Local or regional anaesthesia without general anaesthesia Surgery involving the kidneys (e.g. nephrectomy, partial kidney resection) Chronic kidney disease with eGFR < 15 ml/min or chronical dialysis Surgery utilising cardiopulmonary bypass Emergency surgery Transplant surgery Participation at another interventional trial Insufficient language skills Lacking capacity to consent of patients under legal supervision

*ASA* American Society of Anesthesiologists, *eGFR* estimated glomerular filtration rate

Patients will be screened when they present for routine preoperative evaluation before the scheduled surgery. After written informed consent to participate in this trial is obtained, the patient’s NT-proBNP will be measured in venous blood using a validated point-of-care immunoassay with a measurement range of 60–9,000 pg/mL (proBNP + , cobas h 232; Roche Holding AG, Basel, Switzerland), which yields a result in approximately 10–12 min. If the NT-proBNP level is < 450 pg/mL, further participation in this trial is precluded, and the patients will undergo routine treatment. If the NT-proBNP level is ≥ 450 pg/mL, the patients will undergo 1:1 block randomisation using a computer-generated list implemented in the electronic case report form into a standard care and an intervention care group.

Because evidence for specific NT-proBNP cut-offs triggering distinct treatment strategies is lacking, we conducted a pilot observational study at the anaesthesiology outpatient clinic of the University Hospital of Giessen, where a clinically applicable NT-proBNP cut-off of 450 pg/mL showed a favourable selection of patients at high risk for postoperative morbidity [11]. Specifically, we evaluated the postoperative morbidity of patients with or without known HF, stratified by preoperative NT-proBNP level, which was obtained in the same way and at the same timepoint as it will be in the PeriOP-CARE HF trial.

Patients randomised into the control group will receive routine care according to current guidelines, local standard operating procedures and in line with the attending physicians with no further trial-specific intervention. Patients randomised into the intervention group will receive interdisciplinary, intersectoral, standardised preoperative optimisation and perioperative treatment.

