### Sample size calculation and statistical analyses

The primary end point of this trial has not been used in other studies, and no event rates after 90 days were available for our study cohort. However, overall complication rates between 24.6% and 29.7% have been reported for comparable surgical patient cohorts [13–15]. Therefore, our sample size calculation assumed a 26% event rate. Considering a significance level of 0.05, a two-sided *z*-test (PASS 2020; NCSS, LLC, Kaysville, UT, USA) indicated a sample size of 492 per group to demonstrate an odds ratio of 0.65 in the intervention group with a power of 80%. Considering a dropout rate of 10%, 1094 patients with NT-proBNP levels ≥ 450 pg/mL must be included. Since 37% of the patients evaluated in the pilot study had preoperative NT-proBNP levels ≥ 450 pg/mL, and fewer exclusion criteria were applied, we assumed that 30% of all the included patients would have NT-proBNP levels above the cut-off [11]. Therefore, approximately 3647 patients need to be screened to ensure 547 patients in both the control and intervention groups.

An independent clinical end point adjudication committee will evaluate the primary end point of this trial. All primary and secondary end points will be described using descriptive statistics and compared with t-tests or chi-squared tests, depending on the parameter type. Subsequent outcome analyses will use univariable logistic regression for the primary end point, and multivariable logistic regression will be added to adjust for possible confounding variables. Further analyses will evaluate site-specific effects, and if found, adjustments will be performed.

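### Site is adjusted for only if site effects are found, and the article names no stratification by centre; centre should be fixed in the primary analysis beforehand

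*Protocol article*

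**What the plan says.** All references are to the protocol article.

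- **Study design:** the trial "will be conducted at six university hospitals in Germany".
- **Study population, allocation:** for patients at or above the NT-proBNP cut-off, "the patients will undergo 1:1 block randomisation using a computer-generated list implemented in the electronic case report form". Ratio, method and tool are given. No stratification factor is named.
- **Study population, control arm:** controls receive "routine care according to current guidelines, local standard operating procedures and in line with the attending physicians".
- **Sample size calculation and statistical analyses:** end points are compared with t-tests or chi-squared tests. Univariable logistic regression follows for the primary end point, and a multivariable model is added for possible confounders. On centre, the plan is: "Further analyses will evaluate site-specific effects, and if found, adjustments will be performed".

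**The concern.** Control care is defined locally, and the intervention relies on local staff, so outcome risk may differ between the six hospitals. The sponsor evidently thinks so too, since it plans to look for site effects. Two things follow.

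First, if blocks run across centres, they balance the arms overall but not within each hospital. A chance difference in centre mix then adds noise to an unadjusted comparison, and the site-specific analyses rest on uneven arms.

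Second, the role of site depends on what the data show. If the list is stratified by centre, centre belongs in the primary model whatever a site test finds. If it is not, prespecified adjustment recovers the lost precision. Under either design, making the adjustment conditional is the weaker choice, because the final model then depends on a preliminary test.

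**Working it through.** **Inputs from the article:** six centres; 26% event rate; odds ratio 0.65; two-sided 0.05; 80% power; 492 per group; 10% dropout; 1094 in total. **Not given, so assumed:** centre sizes, block size (4 used here) and centre risks.

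**1. The plan's own figure.** The article states that "our sample size calculation assumed a 26% event rate". With an odds ratio of 0.65, the intervention odds are 0.26/0.74 × 0.65 = 0.2284, so the risk is 0.2284/1.2284 = 18.59%, a difference of 7.41 points. The unpooled z-test gives

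n = (1.960 + 0.8416)² × (0.26×0.74 + 0.1859×0.8141) / 0.0741² = 492 per group.

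Then 492/0.9 rounds up to 547 per group, or 1094 in total. The stated size reproduces, and nothing below changes it.

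**2. Split within a centre, if the list ignores centre.** For a centre of m patients out of N = 1094, the SD of the share on intervention is approximately √[0.25/m × (1 − m/N)].

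- m = 182 (six equal centres): √(0.001374 × 0.834) = 0.0338. Times 1.96 this is 6.6 points, so 43.4% to 56.6%.
- m = 54 (smallest of an assumed 400, 250, 180, 120, 90, 54): √(0.004630 × 0.951) = 0.0663. Times 1.96 this is 13 points, so 37% to 63%.

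Simulation (4,000 trials) gives the same ranges. At least one centre is more than 5 points from 50% in 53% of trials with equal centres and in 78% with the unequal sizes. Lists per centre keep every centre within about 48% to 52%.

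**3. Effect on the overall comparison.** Take control risks spread evenly from 13.5% to 38.5% over six equal centres, a wide spread chosen for illustration. Simulated error from centre mix then has an SD of 0.52 points (95% range about −1.0 to +1.0). The standard error of the risk difference with 547 per arm is √[(0.1924 + 0.1514)/547] = 2.5 points. Centre mix is thus (0.52/2.5)², about 4% of the variance. For a comparison inside one centre, a 57:43 split keeps 4 × 0.57 × 0.43 = 98% of the efficiency of an even split.

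**4. Type I error and power.** Simulation used six centres of 164 (984 patients), blocks of 4, and centre log-odds with SD 0, 0.3 or 0.5. One SD either side of 26% is about 21% to 32% for SD 0.3 and 18% to 37% for SD 0.5 (odds 0.351 multiplied by e^±0.3 or e^±0.5).

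| SD of centre log-odds | Unadjusted power, list ignores centre | Unadjusted power, per-centre lists |
|---|---|---|
| 0 | 0.797 | 0.804 |
| 0.3 | 0.788 | 0.796 |
| 0.5 | 0.780 | 0.773 |

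Each figure rests on 6,000 trials, so its simulation error is √(0.8×0.2/6000) = 0.005. The differences between columns are close to noise. Type I error was 0.050 to 0.053 when the list ignores centre and 0.044 to 0.059 with per-centre lists.

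A separate simulation of the same size compared the analyses under a list that ignores centre. Adjusting for centre raised power from 0.784 to 0.793 (SD 0.3) and from 0.783 to 0.801 (SD 0.5). Adding per-centre lists gained little more. These gains are small and should be read as an order of magnitude.

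**The case against.** **The list.** A reader might infer that one list serves all six hospitals and ignores centre. The article does not say this. A computer-generated list in an electronic case report form can hold separate blocks for each centre, and a condensed article commonly leaves strata and block sizes to the full protocol. The sentence on site effects concerns analysis and is compatible with either design. This objection stands: the list calls for confirmation, and no defect in it is shown.

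**The harm.** The centre-mix error is random and is already covered by the ordinary standard error. A reader might call it bias, but type I error stays near 5%. The centre risks used above are assumed. Nor does the article show centre to be the leading prognostic factor: it ties morbidity explicitly to NT-proBNP and heart failure, whereas for centre it says only that control care follows local procedures. This also stands, and it limits the size of the point.

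**The cost of per-centre lists.** They are not free. Staff know the allocation, so short fixed blocks within a centre make the next assignment easier to guess.

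**The existing plan.** Multivariable regression and conditional site adjustment are already foreseen, so centre may be included in the end. This answers only part of the point. The conditional adjustment is stated text, not an omission, and it is the weaker choice whichever way the list was built.

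**Conclusion.** The point holds in a limited form. What rests on stated text is that the primary comparison is unadjusted and that site is added only if effects are found, in a six-centre trial with locally defined control care. What rests on silence is the structure of the list, and that needs a statement from the sponsor.

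The trial's validity is not in question. If the list ignores centre, the share on intervention ranges by chance over about 43% to 57% in a centre of 182 (blocks of 4), and wider in small centres. The unadjusted test gives up about 1 to 2 points of power if centre log-odds vary with an SD of 0.3 to 0.5. With more similar centres the loss approaches zero. Most of the gain comes from adjusting for centre in the analysis, not from changing the list.

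**What to change.** 1. **Sample size calculation and statistical analyses:** replace the conditional site adjustment with centre prespecified in the primary analysis, by logistic regression with treatment and centre or by a Mantel-Haenszel test stratified by centre, whatever a test of site effects shows. The examination of site-specific effects can remain as a secondary analysis. The cost is one sentence before the data are analysed, with no change to the 492 per group or the 1094 in total. The text should say that the adjusted odds ratio is conditional on centre, since it can lie slightly further from 1 than the unadjusted one.

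2. **Study population:** state whether the randomisation list is stratified by centre. If it is, one phrase suffices.

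3. **Only if it is not, and enrolment has not started:** use one permuted-block list per centre with concealed, randomly varying block sizes in the same electronic module. The cost is new lists and slightly more predictable allocation in an open trial, which varying sizes reduce. The Study design section planned the first enrolment for the end of 2024. If recruitment is already under way, centre would not have been a stratum for the patients already randomised, so step 1 should carry the correction alone.

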### Intervention

The intervention period covers the entire perioperative period, starting immediately after randomisation into the intervention group and ending at the patients’ hospital discharge after surgery. An overview of the treatment interventions during the different perioperative periods is provided in Fig. 2. In addition to standard care, all patients will receive a standardised preoperative evaluation immediately in the anaesthesia outpatient clinic. Therefore, clinical examination by anaesthesiologists and cardiologists is initiated, followed by electrocardiography (ECG) and transthoracic echocardiography. Patients will be screened for depression and anxiety using the Personal Health Questionnaire-9 (PHQ-9) and Generalised Anxiety Disorder-7 (GAD-7) scales, respectively.

**Fig. 2 Fig2:**
[figure not shown]
Multimodal, interdisciplinary, intersectoral perioperative interventions in the intervention group. *EEG* electroencephalogram, *CVP* central venous pressure, *POM*: perioperative management

Once all findings have been collected, the Perioperative Management (POM) board will conduct an interdisciplinary discussion of the patient’s case, and the individual treatment strategy will be determined by consensus. The POM board comprises essential representatives from anaesthesiology, cardiology, the specialist surgery participating in the patient’s treatment and, in the case of pathological findings in the PHQ-9 score (> 14), a psychosomatic physician. Other invited participants are the patient’s general practitioner and the practicing specialist, whose attendance is generally optional. The POM board will be held as a blended meeting, with participants able to attend in-person or online, with the latter especially relevant for ambulatory care physicians, who will most likely be unable to attend in person. To fulfil data protection regulations, the POM board meeting will use a special telemedicine software (AMP.clinic; Awesome Technologies, Würzburg, Germany) with a personalised login, where diagnostic findings, such as echocardiography images and sequences, can be shown to all participants.

The following interdisciplinary decisions for individual perioperative patient management are possible: First, cancel surgery if––despite the best possible preoperative optimisation––it would provide no or only little improvement in the patient’s primary disease and quality of life with a high risk of new physical disabilities and comorbidities; such patients will be transferred to conservative treatment. Second, postpone surgery to further optimise the patient preoperatively, which can be recommended individually according to the findings of the preoperative evaluation. This decision might include, for example, establishing guideline-recommended medical HF therapy and up-titration or cardiac rhythm management, as well as further invasive diagnostic and therapeutic coronary or valve interventions, if necessary. Third, proceed with surgery as scheduled in all other cases, and the POM board may recommend additional individual perioperative strategies, such as intraoperative echocardiography or measurement of the pulmonary artery and capillary wedge pressure.

If no individual recommendations are given, the following strategies will be used for all patients in the intervention group. Arterial blood pressure and dynamic preload parameters, such as pulse pressure or stroke volume variation, will be assessed continuously, either non-invasively or invasively, before anaesthesia induction and together with cardiac stroke volume throughout the surgical procedure. Individualised haemodynamic therapy will be derived from these monitoring items, and critical low cardiac output and intraoperative hypotension must be avoided, defined as mean arterial pressure below 65 mmHg, if not individually specified otherwise. Central venous pressure will also be assessed continuously if a central venous catheter is placed, and processed EEG monitoring will be used to avoid burst suppression states. All further intraoperative strategies are at the discretion of the anaesthesiologist and dictated by the surgical requirements.

Postoperatively, structured monitoring for HF-related complications will be performed during the entire hospital stay. Therefore, an interdisciplinary visit at the patient’s bedside will be initiated during the first 3 postoperative days, comprising an anaesthesiologist, cardiologist, the patient’s surgeon and an HF nurse. The HF nurse will perform structured screening for HF complications at the patient’s bedside and the surgical wards daily on weekdays to recognise emerging HF-related complications before they can impede the patient’s recovery process, such as emergency readmission to an intensive care unit because of congestive decompensation. The HF nurse will focus on the patient’s fluid balance to maintain euvolaemia by considering clinical examination, body weight, diuresis, laboratory parameters and vital signs. In cases of uncertainty, the cardiologist supports the nurse. Lastly, the HF nurse will ensure that the patient’s further HF treatment in outpatient care is continued after discharge from the hospital. Therefore, the HF nurse will contact the patient’s general practitioner to provide a summary of the HF-specific findings, further treatment recommendations by the cardiologist, and to arrange a short-term appointment for the patient with the general practitioner.

